### Peer support

All participants receive standard adult care and may have some contact with PSWs via the Recovery College. Additionally, participants in the PSW+ group receive face-to-face visits from a trained PSW. Each participant in the PSW+ group is assigned a PSW from a nearby community by an administrator in the Peer Support Office. Peer support visits are offered for up to six months after a PSW is assigned to a user. A recipient of peer support will be visited by a PSW at least once on the ward before discharge, and at least three times after discharge. For particularly vulnerable cases (i.e. three or more inpatient stays in the past 12 months), up to six visits can be made. The PSW visits occur per the recipient’s preference, either at home, at a meeting point in the community, or at the hospital when the recipient returns for outpatient visits. The carer may also be engaged in peer support visits, where possible.

The peer support visits delivered by PSWs are flexible and unstructured, and may consist of any or all of the following:
**Befriending** (social contact, supportive listening and encouragement);**Role-modelling** (sharing personal experiences of illness and recovery);**Psychoeducation** (education on recovery principles);**Problem-solving** (discussing current challenges and possible solutions, liasing with providers to resolve issues with medical and social care as needed).

The qualifications, training, supervision and compensation of PSWs as well as quality assurance for peer support visits are detailed in Table 1.

**Table 1 Tab1:** Brain Gain II Peer Support Workers

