#### Hospital days

Hospital days are the number of days spent in psychiatric inpatient care at Butabika over the previous six months. In order to calculate the number of hospital days, dates of entry and departure are extracted from the patient file at the point of referral and six months from referral. An entry may be the result of formal admission or return to the hospital’s premises following an escape. Similarly, a departure may be the result of formal discharge or escape from the hospital’s premises.

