### Analysis

A detailed a priori statistical analysis plan has been drafted in consultation with a biostatistician and covers the baseline, primary and exploratory analyses described below. The plan will be finalised before any data are analysed and is available from the authors upon request. Any departures from the statistical analysis plan must be itemised and clearly justified in study reports.

We will use Stata/SE v15.1 for statistical analysis. All analyses will be performed at the level of the individual. Significance tests will be carried out with two-sided alpha of 0.05, and results will be reported with 95% confidence intervals.

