#### Primary

The primary analyses will compare the six-month change in primary outcomes (hospital days and number of rehospitalisations) between the PSW+ and PSW- groups. We will carry out both intention-to-treat and per-protocol DID analyses for the two primary outcomes, presenting adjusted and unadjusted results [62]. To be included in the per-protocol analysis, participants in the PSW+ arm must receive at least one recorded ward visit and three recorded community visits during the six-month follow-up period [62]. As described above, disability and family support are potential confounders and will be included as covariates in the adjusted analysis.

We will use multivariable linear regression unless the distribution is skewed, in which case we may consider a Poisson or negative binomial regression, or another appropriate method. The impact of the peer support programme on hospital days and rehospitalisations will be estimated through mixed effects models with a random effect to account for correlations among users with the same PSW and fixed effects for access to peer support (PSW+ group versus PSW-group), time (baseline versus follow-up) and the interaction between access to peer support and time. The interaction estimating the change from baseline to follow-up in the PSW+ group relative to change in the PSW- group is the key effect of interest. We will tabulate the results at follow-up and differences from baseline by group with corresponding 95% confidence intervals.

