Unfortunately, a randomized control trial was not deemed acceptable for the purposes of this study. Indeed, researchers in HICs have pointed out that randomisation may be in opposition to the principles of self-determination embraced by peer support programmes [71], though some have carried out successful randomised-controlled trials nonetheless. DID is designed to control for time-invariant and group-invariant confounders, but does not entirely eliminate the possibility of confounding or other types of bias. As noted by Wing, Simon and Bello-Gomez (2018): “The DID design is not a perfect substitute for randomized experiments, but it often represents a feasible way to learn about causal relationships” (pp.453).

The study design outlined in this protocol introduces a risk of bias, as the two study groups differ by district of residence. There is a possibility that unmeasured time- and group-variant factors may differ between districts and confound the relationship between peer support and use of inpatient care. Peer support is only available in four districts of the relatively prosperous Central and Eastern regions near the country’s capital city, Kampala, where Butabika is located. Further, this is not a blinded study, though PSWs responsible for delivering the intervention do not collect study data from their assigned peers, and neither PSWs, M&E Buddies nor the Peer Support Office Administrator have access to admissions data.

In addition, the outcomes compared between groups are limited to those which can be assessed using the hospital’s routinely collected data. Loss-to-follow-up after discharge from inpatient care is a significant issue for Butabika, which PSWs help to remedy through regular visits to the community. The comparison group does not have contact with PSWs after discharge. Therefore, stakeholders deemed it unfeasible to collect primary data from a significant number of participants in the comparison group. The Indian evaluation upon which this study is based faced similar challenges; outcomes could not be assessed in about a third of all participants in the comparison group [43].

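### The primary mixed model names a random effect for the PSW but none for the participant measured twice, so in the linear model the standard error of the key interaction is likely to be too large

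*Protocol article*

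**What the plan says.** The Primary subsection of Analysis writes out both parts of the model. The random part is "mixed effects models with a random effect to account for correlations among users with the same PSW". The fixed part is access to peer support, "time (baseline versus follow-up) and the interaction between access to peer support and time". The target is explicit: "The interaction estimating the change from baseline to follow-up in the PSW+ group relative to change in the PSW- group is the key effect".

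The outcomes are paired. Under Hospital days, "dates of entry and departure are extracted from the patient file at the point of referral and six months from referral", and the rehospitalisation count comes from the same data. The Analysis section adds that "All analyses will be performed at the level of the individual". That names the unit of analysis, not a covariance structure.

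Only one group has PSWs. Under Peer support, "Each participant in the PSW+ group is assigned a PSW from a nearby community". For the others, the Discussion says "The comparison group does not have contact with PSWs after discharge". How PSW- users enter the PSW random effect is not stated.

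For skewed outcomes the same subsection allows a count model or another method.

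**The concern.** With a PSW term only, two values from one person are treated as independent given the PSW. A difference-in-differences estimate gains precision because each person's stable level drops out of the change. The written model keeps that variance in the residual, so its confidence interval does not reflect the gain. The likely cost is missing a real benefit on either primary outcome.

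There is a second, smaller issue. If the PSW effect is an intercept that is constant over time, it also drops out of the change. It can absorb level differences between the neighbourhoods that PSWs serve. It cannot absorb users of one PSW improving together, which is the correlation that matters for the interaction, because the baseline outcomes cover the period before referral.

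**Working it through.** **Inputs.** 126 PSW+ and 87 PSW- users followed up (Study size); two-sided alpha 0.05 (Analysis); 30 PSWs trained (Table 1). Assumed, because the article does not give them: the within-person correlation rho, the PSW-level ICC, and that all 30 trained PSWs are active (126/30 = 4.2 users each).

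**The plan's own figures.** 180 x (1 - 0.15 - 0.15) = 126 reproduces. The 80% power cannot be checked: SD, ICC and baseline-to-follow-up correlation are not in the article, and Additional file 2 is not shown.

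**Step 1: standard error.** With complete pairs the interaction estimate is mean change in PSW+ minus mean change in PSW-. With outcome SD 1 at each time:

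- true variance = 2(1 - rho)(1/126 + 1/87)
- variance if the rows are taken as independent = 2(1/126 + 1/87) = 2 x 0.01943, so SE = 0.1971
- reported SE / true SE = 1/sqrt(1 - rho)

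**Step 2: error rate and power.** Type I error = 2[1 - Phi(1.96/sqrt(1 - rho))]. Where a correct analysis has 80% power, power = Phi(2.802 - 1.96/sqrt(1 - rho)).

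| rho | true SE | reported / true | type I error | power |
|---|---|---|---|---|
| -0.2 | 0.2159 | 0.91 | 7.4% | 84% |
| 0 | 0.1971 | 1.00 | 5.0% | 80% |
| 0.1 | 0.1870 | 1.05 | 3.9% | 77% |
| 0.3 | 0.1649 | 1.20 | 1.9% | 68% |
| 0.5 | 0.1394 | 1.41 | 0.6% | 51% |

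**Step 3: simulation of the linear model.** 1,500 runs per setting, 126 + 87 users, 30 PSWs, PSW variance share 0.05. Entries are reported/true SE and 95% interval coverage.

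| rho | PSW intercept, PSW- one cluster | PSW intercept, PSW- singletons | participant intercept |
|---|---|---|---|
| 0 | 1.01, 94.6% | 1.00, 94.5% | 1.00, 94.7% |
| 0.3 | 1.18, 97.7% | 1.13, 96.5% | 0.98, 94.5% |
| 0.5 | 1.44, 99.5% | 1.33, 99.2% | 1.01, 95.5% |

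The models share the same empirical SE within each setting (0.131 at rho 0.5), so the random-effect choice alters the reported SE and not the estimate. At rho 0.5 and a true effect of 0.39 SD, power is 56% (one cluster), 64% (singletons) and 84% (participant intercept).

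**Step 4: PSW differences in change.** The design effect in PSW+ is 1 + (4.2 - 1) x ICC = 1.16 at ICC 0.05 and 1.32 at 0.10. Applied to the PSW+ part only:

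- sqrt[(1.16/126 + 1/87)/(1/126 + 1/87)] = 1.032
- sqrt[(1.32/126 + 1/87)/(1/126 + 1/87)] = 1.063

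Ignoring this makes the SE too small by about 3% to 6% (type I error 5.8% to 6.5%), against the direction of Step 1. A participant intercept does not remove it. In a harsher setting (rho 0.3, PSW-by-time variance 0.2, an ICC in change of 0.2/(0.2 + 2 x 0.65) = 0.13), coverage with a participant intercept alone was 92.3%.

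**Step 5: Poisson fallback.** A Poisson model without a participant term was simulated at 126/87 with mean 1. Under purely person-level frailty (correlation 0.33), reported/true SE was 0.99 and type I error 5.0%. With added occasion-level overdispersion (correlation 0.38), the ratio was 0.78 and type I error 12%. The negative binomial branch was not computed.

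**The case against.** The article summarises a separate analysis plan, drafted with a biostatistician and not yet final, which may contain a participant term. The outcomes are described as change, and paired tests are planned for exploratory scores, so the authors know that the data are paired. This limits what can be said about the unseen plan. It does not repair the article's model, whose random and fixed parts are listed and whose random part lacks the participant.

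The other objections narrow the point, and they stand:

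- A reader might infer that the PSW term necessarily cancels from the interaction. The text says only a random effect. Cancellation needs a time-constant intercept in a linear model.
- A reader might infer that the term is meaningless for the PSW- users, 87/213 = 41% of those followed up. Coded as singletons, each with two values, they make it act as a participant intercept in that group. The error shrinks but remains.
- A reader might infer that the interval is always too wide, or that false positives are the risk. In the linear model with positive rho the test is conservative. Negative rho, PSW differences in change, or an overdispersed Poisson fit push the other way.
- rho may be low, because eligibility selects on past admissions. At 0.1 the cost is small.

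**Conclusion.** The point holds for the linear model as written. With positive within-person correlation, the SE of the interaction is too large by up to about 1/sqrt(1 - rho), and by less if PSW- users are singletons. At plausible but assumed values of 0.3 to 0.5 the power loss is material for both primary outcomes. The linear point estimate is unaffected with complete pairs. The interval is right only if rho is zero and PSWs do not differ in change, or if the two errors happen to offset.

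The PSW part is secondary. It rests on an intercept reading, an assumed ICC of 0.05 to 0.10 and 30 active PSWs. For the Poisson fallback, the documents support only that the SE may be wrong, with a direction that depends on occasion-level overdispersion.

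**What to change.** Before the analysis plan is finalised:

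1. Add a participant random intercept, or analyse each participant's change. Alternatively, use robust standard errors clustered on participant, which also cover the count models.
2. State how PSW- users enter the PSW term, for example as singletons or with no PSW term.
3. As a sensitivity analysis, put the PSW random effect on the follow-up response in PSW+ only. With about four users per PSW it may be estimated near zero or fail to converge, so the plan should say what is reported then.

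Items 1 and 2 cost a line or two of plan text and code. Item 3 adds one further model. None needs extra data.

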#### Exploratory

Further exploratory analyses will be carried out to help contextualise the results of the main analyses and generate hypotheses for future testing. As primary data collection from the PSW- group is not possible at six-month follow-up, exploratory analyses are limited to the PSW+ group.

##### Disability, service satisfaction and family support outcomes

Likert scale data on disability, satisfaction with services and family support will be collected from the PSW+ group by M&E Buddies at both baseline and six-month follow-up. For both disability and family support, we will calculate summary scores at baseline and follow-up in the PSW+ group [53], then perform a one-sample paired t-test. If the data distribution is skewed, we will consider the Wilcoxon signed-rank test or another non-parametric alternative. For the five-item Likert scale question on service satisfaction, we will use chi-squared tests to test the significance of the difference between baseline and follow-up in the PSW+ group.

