**Training**	
Thirty PSWs from communities in Kampala and nearby districts identified by the user-led organisation HeartSounds Uganda were trained in 2012, prior to the start of Brain Gain II. The five-day training was delivered in Kampala by three mental health professionals from the UK with experience managing peer support programmes. Training covered principles of peer support work, recovery and wellness, communications skills, techniques for managing aggression and using Tree of Life as a tool to positively reframe personal narratives of illness and recovery [31]. In March 2015 the trained PSWs participated in an additional Training of Trainers as part of Brain Gain II, to help build the capacity of new cohorts of PSWs [37]. The Training of Trainers has since been manualised and is available upon request.	

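### The exploratory tests of change in disability and family support ignore shared peer support workers, so their p-values and intervals will be too small if changes are positively correlated within worker

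*Protocol article*

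**What the plan says.** Under Disability, service satisfaction and family support outcomes, the protocol article plans for disability and family support: "we will calculate summary scores at baseline and follow-up in the PSW+ group [53], then perform a one-sample paired t-test". The fallback is also given: "If the data distribution is skewed, we will consider the Wilcoxon signed-rank test or another non-parametric alternative". Neither sentence mentions the PSW.

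Under Primary, the two hospital outcomes are analysed by "mixed effects models with a random effect to account for correlations among users with the same PSW". The grouping comes from the programme itself (Peer support section): "Each participant in the PSW+ group is assigned a PSW from a nearby community by an administrator in the Peer Support Office".

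The opening of the Analysis section applies a two-sided 5% level to significance tests and 95% confidence intervals to results, without exempting the exploratory ones. The Exploratory section states their purpose: "Further exploratory analyses will be carried out to help contextualise the results of the main analyses and generate hypotheses for future testing".

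**The concern.** The same PSW+ users are treated as grouped by PSW in one analysis and as independent in another. The named t-test takes its standard error from the spread of individual changes divided by the square root of the number of users. That is right only if users' changes are uncorrelated. The signed-rank test needs the same condition.

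Some correlation within PSW is plausible here. The Potential confounders section says the baseline form is completed before any PSW visit in the PSW+ group, so any difference between PSWs falls on the change score, which is the quantity tested. The content of visits is left open, so PSWs may differ in what they deliver. PSWs come from near the user, so a caseload may also share a locality.

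At stake are the only significance tests planned for change in disability and family support. If their error bars are too tight, a chance change is more likely to be read as a signal when the primary result is put in context.

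**Working it through.** **Inputs**
- Users with a paired change score: 126, the most that the Study size section expects to complete follow-up in PSW+. It reproduces as 180 × (1 − 0.15 − 0.15) = 126. Losses taken in sequence would give 180 × 0.85 × 0.85 = 130, which barely alters what follows.
- Number of PSWs: Table 1 (Training) says "Thirty PSWs from communities in Kampala and nearby districts" were trained in 2012. It does not say how many carry a caseload, and it mentions later cohorts. Thirty is therefore an assumption; 20 and 15 are shown as alternatives.
- Intraclass correlation (ICC) of the change score: none is given in the article. Values of 0.01 to 0.20 are assumed.

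**Formulas**, for k PSWs with equal caseloads m = 126/k:
- Design effect: DE = 1 + (m − 1) × ICC
- True standard error ÷ reported standard error = √DE
- Real size of the two-sided 5% test = 2 × [1 − Φ(1.96/√DE)]

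**Thirty PSWs**, m = 126/30 = 4.2, so DE = 1 + 3.2 × ICC:

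| ICC | DE | SE ratio | Real size |
|---|---|---|---|
| 0 | 1.00 | 1.00 | 5.0% |
| 0.01 | 1.03 | 1.02 | 5.4% |
| 0.05 | 1.16 | 1.08 | 6.9% |
| 0.10 | 1.32 | 1.15 | 8.8% |
| 0.20 | 1.64 | 1.28 | 12.6% |

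**Simulation check** of the t-test (40,000 runs per row): 4.8%, 5.3%, 6.8%, 9.0% and 12.8%, in agreement with the table. The signed-rank test (4,000 runs) gave 5.2%, 6.4% and 9.2% at ICC 0, 0.05 and 0.10, so the fallback does not escape the problem.

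**Sensitivity to the number of PSWs**
- 20 PSWs (m = 6.3): real size 5.6%, 8.1%, 11.3% and 17.2% at ICC 0.01, 0.05, 0.10 and 0.20.
- 15 PSWs (m = 8.4): 5.9%, 9.4%, 13.7% and 21.3%.
- More than 30: for example 42 PSWs (m = 3) at ICC 0.10 gives DE = 1 + 2 × 0.10 = 1.20 and an SE ratio of √1.20 = 1.10, against 1.15 with 30.

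**Sensitivity to uneven caseloads**, with 30 PSWs and an assumed coefficient of variation (CV) of caseload of 0.6: DE = 1 + [(1 + CV²) × m − 1] × ICC = 1 + (1.36 × 4.2 − 1) × ICC. This is 1.24, 1.47 and 1.94 at ICC 0.05, 0.10 and 0.20, so SE ratios are 1.11, 1.21 and 1.39.

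**Does allowing for PSW repair it?** A t-test on PSW means, simulated with equal or near-equal caseloads, kept its size between 4.9% and 5.2% for 30, 20 and 15 PSWs at every ICC above.

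**The case against.** The strongest reply is that nothing in the article shows the correlation exists for these two scales. The random effect is specified for hospital days and rehospitalisations only, and the ICC scenarios behind the sample size are in an additional file about the primary comparison. The scores are collected by M&E Buddies, and a participant's Buddy is never also their PSW, so a shared assessor is not a route to clustering by PSW. This stands. A reader might infer that the reported p-values are certainly too small, or that the real error rate is around 20%. The article supports neither. The first needs a positive ICC; the second needs something like ICC 0.20 with only 15 active PSWs.

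Second, these analyses are exploratory and have no comparison group. A change from an inpatient baseline to six months cannot be credited to peer support however its standard error is computed. This also stands, and it limits the consequence.

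Third, a separate statistical analysis plan is said to cover the exploratory analyses, and variance details often sit there. This carries less weight: the article does not leave the test open. It names one that conflicts with its own treatment of the same users.

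A reader might also infer from the Discussion sentence "Loss-to-follow-up after discharge from inpatient care is a significant issue for Butabika, which PSWs help to remedy through regular visits to the community" that the paired tests are biased by attrition. The article does not establish that. The sentence helps explain why follow-up interviews were not feasible in the comparison group, and it says that PSW visits reduce the loss. The Missing data section also provides for principled methods above 5% missing. Attrition is no part of this point.

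**Conclusion.** The point holds conditionally. The named tests assume independence among users whom the plan groups by PSW elsewhere. If changes in disability or family support are positively correlated within PSW, the p-values will be too small and the intervals too narrow.

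Under the working assumptions (126 users, 30 active PSWs, equal caseloads), the understatement of the standard error is negligible at ICC 0.01, modest at 0.05 and material from about 0.10 upward. At ICC zero the tests are correct. The number of active PSWs, the spread of caseloads and the ICC are all unstated, so the size is a range and not an estimate.

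This is a minor, worthwhile correction to exploratory results. It does not touch the primary analyses or their conclusions.

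**What to change.** For disability and family support, replace the paired t-test by an intercept-only model of the change score with a PSW random effect, or by the mean change with standard errors clustered by PSW. Report the mean change with its 95% interval. With about 30 PSWs or fewer, use a small-sample reference such as t with k − 1 degrees of freedom. For skewed scores, replace the signed-rank test by a bootstrap that resamples whole PSW caseloads, or by a test on PSW means. The latter weights PSWs equally rather than users, and the text should say so.

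The cost is about one sentence per scale type. The PSW identifier is already needed for the primary models, so no new data are required. Intervals become slightly wider. If the ICC is in fact zero and k = 30, the widening from the t reference is about 3% (2.045 on 29 degrees of freedom ÷ 1.979 on 125 = 1.03).

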### Study size

Brain Gain II aims to enrol 180 users into peer support over six months. Assuming at least a 15% refusal rate and 15% loss-to-follow-up [60], we expect a maximum of 126 participants to complete follow-up in the PSW+ group. With this estimate in mind, we conducted a sensitivity analysis exploring a variety of different scenarios relating to power, effect size and intraclass correlation, allowing for both balanced and unbalanced samples, at 0.05 alpha (see Additional file 2). Results suggest it is possible to detect a clinically meaningful effect (20% as per Cohen [1998]) with 80% power, or a larger effect (30%) with 90% power, if an additional 87 users are followed up in the PSW- group [61]. We therefore aim to recruit at least 129 users to the PSW+ and 101 to the PSW- group.

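### Change in service satisfaction is to be tested with chi-squared tests, although the same PSW+ users answer the same ordered question twice

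*Protocol article*

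**What the plan says.** The protocol article, under Disability, service satisfaction and family support outcomes, lists three measures that "will be collected from the PSW+ group by M&E Buddies at both baseline and six-month follow-up". One group of users is therefore measured twice.

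For two of the three, disability and family support, the plan is to compute summary scores and "then perform a one-sample paired t-test"; if the data are skewed, "we will consider the Wilcoxon signed-rank test or another non-parametric alternative". Both are paired methods.

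The third is handled differently. "For the five-item Likert scale question on service satisfaction", the text continues, "we will use chi-squared tests to test the significance of the difference between baseline and follow-up in the PSW+ group". No paired variant and no ordinal method is named.

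The Exploratory section confines these analyses to the PSW+ group and gives their purpose: "Further exploratory analyses will be carried out to help contextualise the results of the main analyses and generate hypotheses for future testing".

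**The concern.** Pearson's chi-squared test assumes independent observations and treats the response levels as unordered. Here each user contributes two answers, and the levels have an order. There are two ways to build the table, and neither gives a valid test of change:

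- **Time point by response (2 × 5).** Each person is counted twice as if two people had answered. Positive within-person correlation makes the true variance of the change smaller than the test supposes, so the test is conservative and loses power. Ignoring the order costs further power.
- **Baseline by follow-up (5 × 5).** The test then asks whether a person's two answers are related. They usually will be, so it tends to reject whether or not satisfaction has moved.

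The first version can hide a real shift. The second can present ordinary within-person consistency as a change. Either undermines an analysis meant to give context and generate hypotheses.

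**Working it through.** The protocol gives no power or effect size for this test, so there is no figure of its own to reproduce. The check is how the named test behaves under the stated design.

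**Inputs from the protocol**
- Number of pairs: Study size says "we expect a maximum of 126 participants to complete follow-up in the PSW+ group", and 180 × (1 − 0.15 − 0.15) = 126. A smaller number also follows from that section: 129 recruited less 15% loss is 129 × 0.85 ≈ 110.
- Level: "Significance tests will be carried out with two-sided alpha of 0.05" (Analysis section).
- Outcome: one question, read here as having five ordered response levels.

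**Assumptions not in the protocol**
- Within-person correlation of the underlying satisfaction: 0 to 0.85.
- Shift on the underlying normal scale: none, 0.2 SD or 0.3 SD.
- Two baseline distributions over the five levels: 10/20/30/25/15% and 3/7/15/40/35%. Ranges below span the two.

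**Why pairing matters.** For one response level with probability *p* at both times, and probability *q* that a person gives that response both times:

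- variance of the difference in proportions assumed by the 2 × 5 test: 2*p*(1 − *p*)/*n*
- true variance: 2[*p*(1 − *p*) − (*q* − *p*²)]/*n*

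If answers are positively related, *q* > *p*², so the test uses too large a variance.

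**Simulation, n = 126 pairs** (4,000 runs under no change, 2,000 under a shift). Rejections at nominal 5% when nothing has changed:

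| Correlation | Pearson 2 × 5 | Wilcoxon signed-rank | Pearson 5 × 5 |
|---|---|---|---|
| 0 | 4.4–5.0% | 4.6–5.8% | 4.8–6.4% |
| 0.3 | 3.2–3.7% | 4.9–5.4% | 43–54% |
| 0.5 | 2.6–2.8% | 4.6–4.9% | 96–97% |
| 0.7 | 1.2–1.5% | 4.9–5.2% | 100% |
| 0.85 | 0.4–0.6% | 4.6% | 100% |

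Power for a shift of 0.3 SD:

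| Correlation | Pearson 2 × 5 | Stuart-Maxwell (paired, unordered) | Wilcoxon (paired, ordered) |
|---|---|---|---|
| 0 | 36–41% | 34–39% | 56–61% |
| 0.3 | 33–36% | 46–52% | 67–76% |
| 0.5 | 29–34% | 57–65% | 80–86% |
| 0.7 | 25–30% | 78–87% | 93–96% |

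For a shift of 0.2 SD at correlation 0.5, the figures are 11–12%, 27–33% and 46–52%.

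**Smaller sample.** A separate simulation used 110 pairs, underlying cut-points at −1.5, −0.5, 0.5 and 1.5, and 1,500 data sets per setting. At correlations 0.3, 0.5 and 0.7 the 2 × 5 test rejected a true null in 3.7%, 2.3% and 1.2% of runs. Its power for a 0.3 SD shift was 31%, 28% and 22%, against 67%, 81% and 94% for Wilcoxon. The pattern is the same.

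**Splitting the loss.** At correlation 0.5 and n = 126, moving from Pearson to Stuart-Maxwell, which restores the pairing, adds 29 to 31 percentage points (57.4 − 28.8 = 28.6; 64.8 − 33.6 = 31.2). Moving on to Wilcoxon, which also uses the order, adds 21 to 22 (85.7 − 64.8 = 20.9; 79.8 − 57.4 = 22.4). Somewhat more than half of the gap therefore comes from ignoring the pairing.

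**The case against.** The strongest reply is that the phrase is generic. McNemar, Bowker and Stuart-Maxwell statistics are all referred to a chi-squared distribution, and the article is a condensed account with a separate analysis plan that covers the exploratory analyses. The authors may have had a paired version in mind. That is possible, but the article commits to a test by name. It names no paired variant, although it does name paired methods for the two sister outcomes in the preceding sentences. A reader would take it as the ordinary test. Even on the generous reading, a nominal paired test would give up the power shown above.

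Three further points stand and limit the finding:

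- Ignoring the order costs efficiency but is not an error. Treating the levels as nominal is valid if the pairing is respected.
- On the 2 × 5 table the error does not produce false positives under positive correlation, and at low correlation it is mild (3.2 to 3.7% at 0.3). How much power is lost depends on the assumed correlation and shift, and shifts above 0.3 SD were not examined.
- This is one exploratory question in one uncontrolled group. Even a valid before-after test could not attribute a change to peer support, and neither the sample size nor the primary analyses depend on it.

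**Conclusion.** The concern holds. The test named for satisfaction does not suit two answers from the same person. On a 2 × 5 table it is conservative and, at correlations of 0.5 to 0.7, has 25 to 34% power for a 0.3 SD shift that Wilcoxon would detect with 80 to 96% power. On a 5 × 5 table it tests the wrong hypothesis. These figures rest on 126 pairs, a latent normal model, and the assumed correlations, shifts and category distributions. The faults themselves, ignored pairing in one table and the wrong hypothesis in the other, do not depend on those values. The importance is limited by the exploratory, single-group setting, but the point should be corrected.

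**What to change.** Replace the sentence on satisfaction with one stating that the change from baseline to six months will be tested with the Wilcoxon signed-rank test on the paired scores of PSW+ users who answered at both times. If the levels are to be kept nominal, name the Stuart-Maxwell test of marginal homogeneity and accept its lower power.

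The cost is one sentence. No new data are needed, provided that the two answers are linked by participant, as the paired tests for disability and family support already require. The Analysis section says that the statistical analysis plan will be finalised before any data are analysed, so the correction can be made there.
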